### 2.9. Outcome Measure

#### 2.9.1. Feasibility Outcomes

The primary outcomes of the study are feasibility indicators, including recruitment rate, retention rate, adherence rate and data missing rate. Recruitment will be considered successful if more than 70% of eligible students agree to participate. Retention will be considered acceptable if more than 80% of participants complete the intervention. Adherence will be defined as participation in more than 70% of the prescribed training sessions. To account for partial participation, adherence will also be calculated as the proportion of completed training sessions relative to the total number of prescribed sessions. Participants who attend some, but not all, scheduled sessions will therefore be categorized according to their overall attendance percentage. The overall missing data rate is expected to remain below 10% [23,24]. Feasibility thresholds were established based on recommendations for pilot and feasibility trials and commonly used progression criteria in feasibility research [25].

Safety-related outcomes will include the number, type, severity, and relatedness of adverse events occurring during the intervention period. Adverse events will include any undesirable physical or psychological symptoms occurring during or after the HIIT sessions, such as musculoskeletal pain, dizziness, excessive fatigue, nausea, shortness of breath beyond expected exertion, or injury. Events will be categorized as mild, moderate, or severe, and as unrelated, possibly related, or probably related to the intervention. These safety indicators will be used to evaluate whether the Chrono-HIIT programme can be delivered safely among college students with low prior physical activity levels.

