### 2.8. Exercise Intensity Monitoring

Exercise intensity will be monitored using both objective and subjective measures. For an objective measure, participants will wear heart rate monitoring wristbands during all training sessions. Exercise intensity will be maintained at approximately 80–90% of estimated maximal heart rate (HRmax). While for subjective measure, participants will also rate their perceived exertion using the modified Borg Rating of Perceived Exertion (RPE) scale (0–10) immediately after each training session.

Given that the study involves participants with low prior physical activity levels, safety monitoring will be conducted throughout the intervention period. Before each training session, participants will be asked about their current physical condition, including any musculoskeletal pain, illness, dizziness, unusual fatigue, or other symptoms that may affect safe participation. During each session, the principal investigator or trained research personnel will observe participants for signs of exercise intolerance, including excessive breathlessness, dizziness, chest discomfort, nausea, musculoskeletal pain, or inability to maintain correct movement technique. Participants will be instructed to stop exercising immediately if they experience any concerning symptoms.

All adverse events and safety-related incidents will be documented using a standardized adverse event recording form. Information recorded will include the type of event, timing, severity, relationship to the intervention, action taken, and outcome. Serious adverse events, if any, will be reported to the research team and relevant ethics committee in accordance with institutional requirements.

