**Figure 2 healthcare-14-01443-f002:**
[figure not shown]
CONSORT Flow Diagram for the Chrono-HIIT Study.

**Table 1 healthcare-14-01443-t001:** SPIRIT (Standard Protocol Items: Recommendations for Interventional Trials) schedule of enrolment, interventions, and assessment.

Timepoint	Study Period										
	Enrolment	Allocation	Post-Allocation								Close-Out
	2/2026–3/2026	2/2026–3/2026	Week 1	Week 2	Week 3	Week 4	Week 5	Week 6	Week 7	Week 8	5/2026
Enrolment											
Screening	√										
Eligibility	√										
Informed consent	√										
Allocation		√									
Intervention morning group			√	√	√	√	√	√	√	√	
Intervention evening group			√	√	√	√	√	√	√	√	
Control group			√	√	√	√	√	√	√	√	
Assessments											√
Health-related physical fitness		√								√	

**Table 2 healthcare-14-01443-t002:** Detail protocol.

Time	Movements
0:00–0:40	High Knees
0:40–1:00	Rest
1:00–1:40	Jumping lunges
1:40–2:00	Rest
2:00–2:40	Jumping Jacks
2:40–3:00	Rest
3:00–3:40	Bodyweight Squats
3:40–4:00	Rest
4:00–4:40	Burpees
4:40–5:00	Rest
5:00–5:40	Butt kicks
5:40–6:00	Rest
6:00–6:40	Push ups
6:40–7:00	Rest
7:00–7:40	Mountain Climbers
7:40–8:00	Rest

**Table 3 healthcare-14-01443-t003:** Interview guide.

No.	Interview Question
1.	Please describe your experience participating in the HIIT course.
2.	What was the most memorable movement for you throughout the entire module? Why?
3.	During the training, what specific physical changes did you notice? (e.g., fatigue level, heart rate, amount of sweating, muscle sensation)
4.	What impact do you think the HIIT has had on your physical fitness, endurance, or overall physical condition?
5.	How did you typically feel emotionally after participating in HIIT? (e.g., excited, stressed, focused, bored).
6.	During or after the training, did you experience any changes in your sense of accomplishment, motivation, self-confidence, or willpower? Please describe specifically
7.	Were there moments when you felt anxious, apprehensive, or wanted to give up? How did you cope with them?
8.	Do you think the current structure, duration, intensity, and movement arrangement of the HIIT module are reasonable? Why?
9.	What do you think are the advantages and potential disadvantages of this training method, respectively?
10.	Regarding safety, what areas do you think require special attention or need more guidance?
11.	Do you have any suggestions?

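### Psychological symptoms count as adverse events, but no stated routine check asks about them, so they are likely to be under-counted

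*Protocol article*

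**What the plan says.** Section 2.9.1 defines the safety outcome and its scope: "Safety-related outcomes will include the number, type, severity, and relatedness of adverse events occurring during the intervention period", and then "Adverse events will include any undesirable physical or psychological symptoms occurring during or after the HIIT sessions". All the examples that follow this definition are physical.

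Section 2.8 describes how events are looked for:
- Before a session: "Before each training session, participants will be asked about their current physical condition, including any musculoskeletal pain, illness, dizziness, unusual fatigue", closing with "or other symptoms that may affect safe participation".
- During a session, staff "observe participants for signs of exercise intolerance, including excessive breathlessness, dizziness, chest discomfort, nausea, musculoskeletal pain, or inability to maintain correct movement technique". In addition, "Participants will be instructed to stop exercising immediately if they experience any concerning symptoms".
- After a session, the one stated measure is the 0–10 Borg rating of exertion.

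The same section sends all adverse events to a standardized form. Section 2.7 also has events and discomfort during training documented.

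Table 3, the interview guide, does ask about emotional reactions. Question 5 asks how participants felt emotionally after HIIT and offers stress as one prompt. Question 7 begins "Were there moments when you felt anxious, apprehensive, or wanted to give up". Section 2.1 limits the interviews to a purposive sample of those who completed the intervention, and section 2.3 puts their number at about 10 to 15.

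**The concern.** The outcome as defined is wider than the means stated for finding it. A physical symptom is asked about by name before each session and watched for during it. A psychological symptom is named in no routine check, although the authors thought such reactions worth asking about at interview.

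The Introduction makes safety part of the primary objective, and the Discussion relies on systematic adverse event monitoring to judge whether the programme is safe and acceptable before a larger trial. If psychological events are seldom recorded because they are seldom asked about, the safety table may look reassuring while the interviews describe distress, and a reader could not tell absence from non-detection. The interviews cannot fill the gap. They reach a minority, and anyone who left because of distress falls outside the group from which interviewees are drawn.

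**Working it through.** The article states no expected adverse event count or rate, so there is no figure to reproduce. The check is a comparison of the text, then a count of who is asked directly, then an illustration of what a zero could mean.

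**1. Definition against checks**

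| Stage | Stated check | Does it name a psychological symptom? |
|---|---|---|
| Before session (2.8) | Question on physical condition, with a closing clause on other symptoms affecting safe participation | No; possible only through the closing clause |
| During session (2.8) | Observation of listed signs, all physical or technical; instruction to stop for concerning symptoms | No; possible if volunteered |
| After session (2.8) | Exertion rating | No |
| After the programme (Table 3, questions 5 and 7) | Interview | Yes, in a subset of completers |

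The definition covers symptoms during or after sessions. The pre-session question asks about the participant's condition at that moment, so a symptom that followed one session and resolved before the next is not clearly covered either.

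**2. Reach of the direct questions**

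- HIIT participants: 24 + 24 = 48 (section 2.3).
- Interviewed: 10/48 = 20.8% to 15/48 = 31.3%. The number may rise if new themes keep emerging (sections 2.3 and 2.10).
- Not interviewed: 48 − 15 = 33 to 48 − 10 = 38, or 69% to 79%.
- Planned sessions: 3 per week × 8 weeks = 24 each, so 48 × 24 = 1,152 person-sessions with no stated question that names a psychological symptom.

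**3. What a zero count could mean (illustration; p and s are assumptions)**

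Let p be the true share of HIIT participants with a psychological symptom that meets the definition, and s the chance that such a participant is recorded. Participants are taken as independent. Then the expected number recorded = 48 × p × s, and P(none recorded) = (1 − p × s)^48. For example, with p = 0.20 and s = 0.10, the expected number is 48 × 0.02 = 0.96, and P(none) = 0.98^48 = 0.379.

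Each cell gives the expected number recorded; P(none recorded):

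| Capture s | p = 5% | p = 10% | p = 20% |
|---|---|---|---|
| 10% | 0.24; 0.786 | 0.48; 0.617 | 0.96; 0.379 |
| 25% | 0.60; 0.547 | 1.20; 0.297 | 2.40; 0.085 |
| 50% | 1.20; 0.297 | 2.40; 0.085 | 4.80; 0.006 |
| 90% | 2.16; 0.110 | 4.32; 0.011 | 8.64; <0.001 |

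With weak capture, an empty record is quite compatible with symptoms in 5% to 20% of participants. With strong capture, it would be informative at p = 10% or 20%. The article fixes neither p nor s, so the count cannot be interpreted as it stands.

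**The case against.** The strongest reply is that the monitoring text is not closed. Both lists in section 2.8 are introduced as examples. The pre-session question ends with a clause on other symptoms, the instruction to stop is not restricted to physical symptoms, trained staff observe the sessions, and every adverse event goes on the form whatever its type. All of this stands. A reader might infer from the mismatch that the psychological count will be near zero by construction, that participants are never asked anything relevant, or that a distressed student would go unnoticed. The documents support none of these. A volunteered symptom has a route to the form, and the table above shows that a near-zero count needs low incidence or low capture. What remains is narrower: the closing clause follows a question about physical condition and is limited to symptoms bearing on safe participation, so the definition is still wider than what is asked.

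A second reply concerns the interviews. A reader might infer that their content is barred from the adverse event record. It is not; the link is simply unstated, the content of the form is not shown, and an article may leave both to the full protocol. That silence is no defect. Nor is every admission of apprehension or of wanting to stop during hard exercise an adverse event. Interviews that add what counts miss are also part of the purpose of a mixed-methods design.

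A third reply is that little turns on the number. Section 2.9.1 sets no adverse event threshold, and none of its numerical feasibility criteria uses a psychological count. This is correct, and it keeps the point minor.

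**Conclusion.** The point holds as a mismatch between section 2.9.1, which counts psychological symptoms as adverse events, and section 2.8, whose routine checks name none. Such events rest on an open-ended clause or spontaneous report, so under-counting is likely, and a low or zero count would not show psychological safety. Direct questions are planned for about 21% to 31% of HIIT participants, all of them completers.

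The amount of under-counting is unknown. The illustration depends on assumed values of incidence and capture, and no single pair of values should be taken as a forecast. The conclusion about ascertainment needs only the text of the two sections and assumes that the article describes the routine checks as they will be carried out.

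**What to change.** Reconcile sections 2.8 and 2.9.1:

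- Extend the existing pre-session question from physical condition to physical or emotional condition, now and since the last session, with a prompt such as anxiety or distress linked to training.
- Record answers that meet the definition in section 2.9.1 on the existing adverse event form.
- Report symptoms first mentioned at interview separately, labelled by source, and keep them out of the routinely ascertained count. They are recalled answers from a purposive 21% to 31% of HIIT participants, and adding them would mix two methods of ascertainment.

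This changes only what is asked and recorded; it sets no clinical rule. The cost is one added prompt, a few seconds per session, and more mild events on record. The report should say that events were solicited in this way, so that a higher count is not mistaken for higher risk.

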To address this research gap, the present study developed a structured HIIT module specifically designed for Chinese college students. Before implementing large-scale intervention programmes, it is essential to evaluate the feasibility and practicality of the training module within the target population. Feasibility studies play a critical role in the early stages of intervention development by assessing recruitment, adherence, acceptability, and implementation challenges within real-world contexts [14]. In addition to quantitative assessments of health-related physical fitness outcomes, qualitative methods such as semi-structured interviews can provide valuable insights into participants’ experiences, perceived benefits, and potential barriers related to the intervention.

Therefore, the present study aims to evaluate the feasibility and preliminary effect of an eight-week time-specific high-intensity interval training (Chrono-HIIT) programme among low-physically active Chinese college students with an intermediate chronotype. The primary objective of this feasibility pilot randomized controlled trial is to assess the practicality and acceptability of implementing the intervention, including participant recruitment, retention, adherence, safety, and data completeness. The secondary objective is to explore the preliminary effects of morning versus evening HIIT on health-related physical fitness outcomes, including body composition, cardiorespiratory fitness, muscular strength, muscular endurance, and flexibility. In addition, the qualitative component of the study aims to explore participants’ experiences, perceived benefits, barriers to participation, and overall acceptability of the intervention. It is hypothesized that the Chrono-HIIT programme will demonstrate acceptable feasibility and adherence among low-physically active Chinese college students and may produce preliminary improvements in health-related physical fitness outcomes. The findings may contribute to the optimization of physical education programmes and inform the design of future large-scale randomized controlled trials aimed at promoting efficient and sustainable physical activity interventions in college settings.

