To ensure intervention fidelity and adherence, attendance will be recorded for each training session. Participants will also be verbally encouraged to maintain the required exercise intensity during the intervals. Any adverse events, discomfort, or injuries occurring during the training sessions will be documented and monitored throughout the intervention period to ensure participant safety.

*Cool-down Phase*

Following completion of the HIIT session, participants will perform a brief cool-down phase consisting of relaxation exercises and static stretching. The primary aim of the cool-down is to gradually reduce cardiovascular demand and facilitate physiological recovery after high-intensity activity [21].

The cool-down routine includes static stretching exercises targeting the major muscle groups involved during the training session, particularly the lower extremities and upper body. These stretches help relieve muscle tension, restore normal muscle length, and improve flexibility following vigorous exercise [22].

Overall, the cool-down phase is designed to promote post-exercise recovery and minimise the likelihood of delayed onset muscle soreness or exercise-related discomfort.

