Upper- and lower-body muscular strength will be assessed using one-repetition maximum (1RM) tests for the chest press and leg press, respectively. The 1RM test is a widely accepted method for evaluating maximal dynamic muscular strength and has demonstrated good reliability in healthy young adults [28]. Both tests will be conducted using fixed resistance machines, thereby minimizing movement instability and reducing the risk of exercise-related injury. Prior to formal testing, participants will attend a familiarization trial to practice the testing procedures and movement techniques. Participants will be screened for musculoskeletal contraindications before maximal strength testing. All tests will be supervised by trained personnel to ensure proper lifting technique and participant safety.

Before testing, participants will complete a standardized warm-up consisting of light aerobic activity followed by dynamic stretching to prepare the muscles for maximal effort.

For the chest press test, participants will perform the exercise using a resistance machine while maintaining proper body alignment and controlled movement technique. For the barbell back squat, participants will stand with feet shoulder-width apart and descend until the thighs are approximately parallel to the floor, while maintaining correct posture and spinal alignment.

The testing load will be progressively increased until the participant can complete only one repetition with proper technique, which will be recorded as the 1RM value. Participants will be given 3–5 min of rest between attempts to minimize fatigue. In most cases, the maximal strength value will be determined within three to five attempts.

If a participant fails to complete a repetition with proper technique, the load will be reduced following an adequate rest period and another attempt will be performed. The highest successfully lifted load (kg) will be recorded as the participant’s upper-body strength (chest press 1RM) and lower-body strength (squat 1RM).

*Muscular Endurance Assessment*

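### Adverse events are sought only around HIIT sessions, so controls and about 96 of 144 planned test visits have no stated route of capture

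*Protocol article*

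**What the plan says.** The Introduction sets out the primary objective as practicality and acceptability, "including participant recruitment, retention, adherence, safety, and data completeness". Section 2.9.1 then lists the primary outcomes without safety: "The primary outcomes of the study are feasibility indicators, including recruitment rate, retention rate, adherence rate and data missing rate". It treats safety in a separate paragraph.

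That paragraph gives the reporting period: "Safety-related outcomes will include the number, type, severity, and relatedness of adverse events occurring during the intervention period". It goes on to describe an event: "Adverse events will include any undesirable physical or psychological symptoms occurring during or after the HIIT sessions". Events are to be graded for severity and for relatedness, with an unrelated category available, and used to judge whether the programme is safe to deliver.

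The collection steps are in two places. Section 2.7 says "Any adverse events, discomfort, or injuries occurring during the training sessions will be documented". Section 2.8 says "Before each training session, participants will be asked about their current physical condition", and has staff watch participants during each session. Section 2.8 also has a broader rule: "All adverse events and safety-related incidents will be documented using a standardized adverse event recording form".

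On testing, section 2.9.2 says "Upper- and lower-body muscular strength will be assessed using one-repetition maximum (1RM) tests". It also plans an arm hang and a wall sit, each held until the participant can no longer keep position. Strength tests are supervised and preceded by screening and familiarisation, but the section does not mention recording events.

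**The concern.** A safety assessment depends on who is asked, when, and about what. Here all three are described through the training session, which only the two HIIT arms attend. The broad rule in section 2.8 says where an event is written down once known. It does not say how an event in a control, or at a test visit, becomes known.

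Three things are at stake. First, maximal lifts and holds to failure in low-active students are a plausible source of strains and soreness, and these could go unrecorded. Secondly, any per-arm table would compare arms observed up to 24 times with an arm not observed at all. Thirdly, the listed complaints (muscle pain, fatigue, dizziness, nausea) also occur without training. Staff must grade their relatedness with no background rate, although a randomised control arm is present that could give one.

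**Working it through.** **Inputs.** 72 participants, 24 per arm (section 2.3), so 48 in HIIT and 24 controls; 3 × 24 = 72 reproduces the planned total. Three sessions a week for eight weeks (Abstract). Fitness tests at baseline and in week 8 (Table 1), with baseline tests completed before randomisation (sections 2.1 and 2.6). The document gives no adverse event rate and no safety threshold.

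**Observation by arm.** Sessions per HIIT participant: 3 × 8 = 24. Planned participant-sessions with enquiry and observation: 48 × 24 = 1,152 in the HIIT arms and 24 × 0 = 0 in controls.

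**Test visits against the description.** Taking one test visit per time point, there are 72 × 2 = 144.

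| Visits | Number | In the intervention period? | During or following HIIT sessions? | Stated capture |
|---|---|---|---|---|
| Baseline, all arms | 72 | No, before randomisation | No | None |
| Week 8, controls | 24 | Yes | No, they have none | None |
| Week 8, HIIT arms | 48 | Yes | Yes, read literally | Arguable |

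Clearly uncovered: 72 + 24 = 96, and 96/144 = 67%. The 1RM familiarisation trial also precedes formal testing and has no stated capture; it is not in this count.

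**What the HIIT arms can still show.** With zero events among n participants, the one-sided 95% upper bound on per-participant risk is 1 − 0.05^(1/n). For n = 48 this is 6.1%; for one arm of 24 it is 11.7%. The chance of seeing at least one event is 1 − (1 − p)^48. Over an assumed range of true risk p of 2%, 5% and 10%, this gives 62%, 91% and 99%. A descriptive summary is therefore informative without control data.

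**The background-rate question.** Its size cannot be computed from the document. As an illustration only, if 10% to 25% of students had one of the listed symptoms over eight weeks for reasons other than training, 48 × 0.10 = 4.8 to 48 × 0.25 = 12 HIIT participants would report one. Each would have to be graded for relatedness without a comparator.

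**Those who stop attending.** Enquiry before sessions reaches attenders only. If the retention criterion (more than 80%) is applied to the HIIT arms, 39/48 = 81% still passes, so up to 9 could leave. No event enquiry at withdrawal is described, and the interviews sample completers (section 2.1).

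**The case against.** The strongest reply is that the text is inclusive. Section 2.9.1 says that events will *include* session-related symptoms, sets no window for what follows a session, and reports over the whole intervention period. Section 2.8 requires all events and incidents to be recorded, without limit by arm or visit. This stands against a stronger reading that a reader might infer: that controls can have no event by definition. The document does not say so. What survives is narrower. No step is described by which a control's event, or one at a baseline test, would be found.

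A reader might also infer that every test visit is excluded. That fails too, because week-8 tests of HIIT participants fall in the intervention period and follow HIIT sessions. Nor are all the tests maximal: the step test is described as submaximal.

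A further reply is that the stated purpose is to judge delivery of the programme, summarised descriptively, with no between-arm safety comparison planned. That is correct, and the 1,152 planned participant-sessions serve the purpose. A control rate would help to interpret relatedness but is not a condition for that summary.

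Finally, a journal article condenses, and procedures for controls may sit in a fuller document. That would excuse silence. Here, however, the article positively states a description and a set of collection steps, and both are one-sided. An analysis plan cannot later recover events that nobody asked about.

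**Conclusion.** The point holds as a gap in ascertainment that should be closed before data collection. Read as written, events are actively sought in 48 of 72 participants and only around training. About 96 of 144 planned test visits, including all baseline 1RM testing, have no stated capture. The broad recording rule in section 2.8 does not fit the session-based wording in sections 2.7 and 2.9.1, and the three need to be reconciled.

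A reader might conclude that the safety part of the primary objective cannot be judged at all. The document does not support that, because the HIIT arms still give a usable descriptive summary. No figure in the protocol changes.

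The count assumes one test visit per person at each time point and full attendance. The risk values and the 10% to 25% background range are assumptions, and the conclusion does not depend on them.

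**What to change.** Reconcile sections 2.7, 2.8 and 2.9.1 as follows.

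- Define an adverse event as any undesirable symptom or injury, in all three arms, from the first trial test to the end of the week-8 tests.
- Use the existing recording form at each test visit, for every arm.
- At week 8, ask every participant one identical standard question about events since the programme period began. Include those who stopped attending, where they can be reached.
- Report by arm, showing separately the events at testing, those observed at sessions, and those from the common week-8 question. Compare arms only on the common question, because the HIIT arms are seen far more often.

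The cost is a few sentences of protocol text, a split in one table, and a few minutes at visits that already take place, plus an attempt to contact those who left. The change concerns data collection and reporting only. Its limit is that recall over eight weeks is less complete than enquiry at each session, so the control figure is only a rough background rate.
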